### Safety Monitoring

2.9

Acupuncture and olfactory therapy pose mild adverse effects. Acupuncture may cause pain, numbness, or bruising, while olfactory therapy may lead to allergic reactions or affect the liver or kidneys. Serious adverse events will be promptly reported, and patients experiencing such events will be withdrawn from the study. Adverse events will be documented on case report forms and reported to statisticians.

Adverse events (AEs) are typically classified into three severity grades: mild, moderate, and severe. Mild adverse events refer to symptoms that are tolerable to participants, requiring no specific intervention, and do not affect the trial progression or participant prognosis. Moderate adverse events involve clinically significant symptoms that are difficult for participants to tolerate, potentially necessitating trial discontinuation or medical treatment, and may impact disease recovery. Severe adverse events are life‐threatening conditions that could lead to permanent disability or mortality, requiring immediate trial termination and emergency medical intervention. During the treatment period, any adverse events must be documented in real‐time, investigated for causality, and promptly reported to the supervising physician for evaluation and management.

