**Methods:**

This parallel‐group, assessor‐blinded, randomized controlled trial will recruit 210 PSCI patients, randomly assigned to one of six groups: control, EA, HOT, combination therapy, sham therapy, or the healthy (ratio 1:1:1:1:1:1). All participants will receive standard cognitive training and basic medical care. The EA group will receive 4 weeks of electro‐acupuncture at specific acupoints. The HOT group will receive 4 weeks of aromatic inhalation therapy using Acorus tatarinowii volatile oil. The combination group will receive both interventions. The primary outcome measure is cognitive function, assessed using the Montreal cognitive assessment (MoCA) at baseline, week 4, and week 8. Secondary outcomes include the mini‐mental state examination (MMSE), functional magnetic resonance imaging (fMRI), near‐infrared spectroscopy (fNIRS), and anxiety assessment using the state‐trait anxiety inventory (STAI) at baseline and week 4. Data analysis will be conducted using a modified intention‐to‐treat approach.

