#### Primary Outcomes

2.7.1

Participants' cognitive abilities will be assessed at three‐time points: baseline (week 0), during treatment (week 4), and follow‐up (week 8) (Table 2). The primary outcome measures include the Montreal Cognitive Assessment (MoCA), which are commonly used tools for evaluating cognitive function across different types of impairment.

**TABLE 2 brb370631-tbl-0002:** Schedule of enrollment, intervention, and assessment.

	Week 0 (baseline)	Week 4	Week 8
MMSE	X	X	X
MoCA	X	X	X
MBI	X	X	X
TCD	X	X	
fNIRS	X	X	
fMRI	X	X	
STAI	X	X	
Adverse Effects			

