#### Secondary Outcomes

2.7.2

The mini‐mental state examination (MMSE): MMSE score will be assessed at three‐time points: baseline (week 0), during treatment (week 4), and follow‐up (week 8).The Modified Barthel Index (MBI): MBI scores will be utilized to evaluate patients' activities of daily living and their level of dependency. It will be assessed at three‐time points: baseline (week 0), during treatment (week 4), and follow‐up (week 8).Transcranial Doppler (TCD)

TCD involves the following steps: First, prepare the equipment, including the transcranial Doppler ultrasound device and the probe, ensuring that the device is properly calibrated and the appropriate parameters are set. Second, prepare the patient or subject, who is typically placed in a supine or sitting position, with ultrasound coupling gel applied to the scalp to ensure sound wave conduction, and the detection points are marked. Finally, detect the cerebral vessels by selecting the appropriate detection window (such as the temporal window, occipital window, and ophthalmic artery window), and adjust the probe angle and position to locate the target cerebral vessels.

Parameter settings: The light source wavelength typically employed ranges from near‐infrared light of 650 to 900 nm, as this range exhibits low absorption of light by both hemoglobin and water. The light source can be either a pulsed laser or an ultra‐short pulsed laser. Detection is performed using a Time‐Correlated Single Photon Counting (TCSPC) detector, which allows for time resolution at the picosecond (ps) level to measure the time of flight of photons. The probe layout generally maintains a distance of 2 to 4 cm between the light source and the detector.

Analysis method: Temporal point spread function (TPSF): This method involves analyzing the time‐of‐flight distribution of photons to derive the optical characteristics of tissue, specifically the absorption coefficient and scattering coefficient. Differential Pathlength Factor (DPF): This factor is employed to correct the path length of photons traveling through tissue. Calculation of Hemoglobin Concentration: The concentration changes of oxygenated hemoglobin (HbO2) and deoxygenated hemoglobin (HbR) are calculated based on variations in the absorption spectrum.
4Near‐infrared spectroscopy (fNIRS)

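### Section 2.9 ties withdrawal from the study to a serious adverse event without separating stopping treatment from leaving follow-up, so primary-outcome visits still due may be lost

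*Protocol article*

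**What the plan says.** Section 2.9 (Safety Monitoring) sets the rule: serious adverse events are to be reported without delay, and "patients experiencing such events will be withdrawn from the study". The rule is mandatory, is not limited to events related to treatment, and names the study rather than the treatment as what the patient leaves.

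The next paragraph of Section 2.9 grades adverse events. A moderate event may lead to trial discontinuation or medical treatment. A severe event, described as life-threatening, calls for immediate trial termination and emergency care.

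The section also provides for safety handling: "Adverse events will be documented on case report forms and reported to statisticians", and events in the treatment period are to be "investigated for causality, and promptly reported to the supervising physician for evaluation and management".

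The primary outcome is cognitive function, "assessed using the Montreal cognitive assessment (MoCA) at baseline, week 4, and week 8" (Abstract, Methods; also Section 2.7.1). Section 2.7.2 and Table 2 put MMSE and MBI at the same three visits. The intervention lasts 4 weeks (Section 2.1), so week 8 falls after treatment. The Abstract names a modified intention-to-treat analysis, and Section 2.1 allows for 10% dropout.

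**The concern.** A patient can stop an intervention and still be assessed. A rule that sends the patient out of the study gives up both the treatment and the outcome data. Here the trigger is a post-randomisation event that may be connected with the treatment received, the patient's prognosis, or both. If the number lost, or the outcomes of those lost, differ between arms, the patients who remain are no longer the groups formed by randomisation, and the MoCA comparison can be biased.

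The article gives some reason to think losses could be unequal. The Introduction attributes significant adverse effects to drug treatment of PSCI, and Section 2.6.1 gives the control group donepezil. The Discussion credits the tested therapies with minimal side effects. This is only a reason to guard against imbalance and does not show that there will be any.

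The loss is also partly avoidable. The visits are already scheduled, and for an event between weeks 4 and 8 the 4-week intervention is over, so withdrawal at that point removes data and little else. Analysis cannot recover a visit that was never made. The repeated-measures ANOVA in Section 2.11, in its usual form, needs complete visits, so a missing week-8 value can also take that patient's week-4 value out of that analysis.

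**Working it through.** **1. The plan's own figure on lost patients.** Section 2.1 raises 32 per group to about 35 for 10% dropout. Check: 32 / (1 − 0.10) = 35.6, so the stated figure is reproduced to within rounding. With 35 enrolled and 10% lost, 35 × 0.90 = 31.5 remain. The allowance deals with numbers. It does nothing about which patients are lost.

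**2. Assessments at stake per patient, from Table 2.**
- MoCA, MMSE and MBI at weeks 4 and 8: 3 × 2 = 6.
- TCD, fNIRS, fMRI and STAI at week 4 only: 4.
- Withdrawn before week 4: 6 + 4 = 10 post-baseline assessments lost, including both MoCA values.
- Withdrawn between weeks 4 and 8: 3 lost (MoCA, MMSE and MBI at week 8).

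These are upper counts, since a patient too ill to be tested would miss some of them under any rule.

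**3. Number of patients affected.** The document gives no serious-event rate. On assumed rates of 1%, 2%, 5% and 10%, the expected number per arm of 35 is 0.35, 0.7, 1.75 and 3.5. If these losses came on top of the 10% dropout, 35 × (1 − 0.10 − rate) would leave about 31.2, 30.8, 29.8 and 28.0.

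**4. Illustration of bias, on assumptions only.** Suppose k of 35 patients in an arm are lost and their mean MoCA change would have been d points worse than that of the patients who remain. The observed arm mean is then too favourable by (k / 35) × d.
- k = 1, d = 1: 1/35 × 1 = 0.03 points.
- k = 2, d = 5: 2/35 × 5 = 0.29 points.

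Between two arms the bias is (k1 × d1 − k2 × d2) / 35. With d = 3 in both arms:

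| Lost, arm 1 | Lost, arm 2 | Bias (MoCA points) |
|---|---|---|
| 2 | 0 | (6 − 0)/35 = 0.17 |
| 2 | 1 | (6 − 3)/35 = 0.09 |
| 1 | 1 | (3 − 3)/35 = 0 |

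One to two of 35 corresponds to 2.9% to 5.7% of an arm. Neither that rate nor d can be checked against the document, which also gives no MoCA change or standard deviation against which to judge the result.

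**5. The wording within Section 2.9.** Three phrases describe an exit: withdrawal from the study (serious), trial discontinuation (moderate) and immediate trial termination (severe). None says whether assessments continue. Changing only the first would leave a participant who stays in follow-up under one sentence and has trial participation terminated under another.

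**The case against.** The strongest reply is that the section uses its terms loosely. Taken literally, immediate trial termination after one patient's severe event would end the whole trial, which cannot be meant. Withdrawal from the study might likewise be shorthand for stopping the intervention. This stands in part: the article does not say in words that visits stop, and staff may in practice go on assessing such patients. But the sentence as printed directs withdrawal from the study, and loose terms are a reason to fix all three phrases.

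A second reply is that a condensed article need not describe follow-up after withdrawal. That is right, and silence alone would be no finding. The point rests on the rule that the article does state.

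Third, the avoidable loss is limited. The article expects mild effects from acupuncture and olfactory therapy. If serious here means what the severe grade describes, many of these patients could not complete a MoCA. This stands, and it limits the weight of the point.

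A reader might go further and infer that safety follow-up ends at the event, or that the MoCA comparison will be biased. The documents support neither. Section 2.9 provides for recording, causality assessment and management of adverse events, and nothing shows that losses will be frequent or unequal.

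**Conclusion.** The point holds as a defect of wording with a possible consequence for the primary outcome. As written, Section 2.9 takes patients with a serious event out of the study, and uses similar language for moderate and severe events, without keeping treatment and follow-up apart. Followed literally, it costs up to 10 post-baseline assessments per patient, in a trial that states a modified intention-to-treat approach.

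The effect is probably small and cannot be sized from the document. The illustrative 0 to 0.17 MoCA points between arms rests on assumed losses of 0 to 2 patients per arm of 35 and an assumed 3-point gap. It is zero if losses and gaps are equal. Confidence is medium, because the reading depends on taking loosely worded text at its plain meaning. The change is worth making because it is cheap and because data not collected cannot be recovered at analysis.

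**What to change.** Replace the serious-event sentence in Section 2.9 with:

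> Serious adverse events will be promptly reported. Study treatment will be stopped where clinically needed. The participant stays in follow-up for the scheduled week-4 and week-8 MoCA, MMSE and MBI and for adverse-event follow-up, unless consent is withdrawn or assessment is impossible, and is analysed in the assigned arm.

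In the severity definitions of the same section, change *trial discontinuation* (moderate) to *discontinuation of study treatment*, and *immediate trial termination* (severe) to *immediate stop of study treatment*. Without this second change the section would contradict itself and the same exit route would stay open.

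The cost is a few words of protocol text and keeping visits that are already scheduled for a small number of patients. No extra patients are needed, and clinicians remain free to stop treatment. The downside is that some assessments will be made off treatment.

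### Section 2.9 ties reporting and withdrawal to 'serious' events, but its printed severity scale leaves some events ungraded and reserves 'severe' for life-threatening ones

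*Protocol article*

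**What the plan says.** Section 2.9 (Safety Monitoring) has two paragraphs that bear on this.

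The first names the expected risks: pain, numbness or bruising from acupuncture, and allergic reactions or liver or kidney effects from the olfactory therapy. It then sets a rule: "Serious adverse events will be promptly reported, and patients experiencing such events will be withdrawn from the study".

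The second says that adverse events "are typically classified into three severity grades: mild, moderate, and severe" and defines each grade:

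- Mild: "symptoms that are tolerable to participants, requiring no specific intervention, and do not affect the trial progression or participant prognosis".
- Moderate: clinically significant symptoms that are "difficult for participants to tolerate, potentially necessitating trial discontinuation or medical treatment, and may impact disease recovery".
- Severe: "Severe adverse events are life‐threatening conditions that could lead to permanent disability or mortality", described as "requiring immediate trial termination and emergency medical intervention".

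The paragraph closes by having every adverse event during treatment recorded as it happens, assessed for cause and passed promptly to the supervising physician. The word *serious* does not appear in the second paragraph, and *severe* does not appear in the first.

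**The concern.** Severity (how intense an event is) and seriousness (what it leads to) are separate attributes, and a safety report needs both. Section 2.9 attaches its operative rule to seriousness, then prints a scale called severity whose top grade is built from seriousness outcomes: threat to life, permanent disability, death. The scale therefore has no grade for high intensity as such, and its lower grades are not worded so that they meet.

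What is at stake is whether adverse events can be graded the same way by different investigators and tabulated meaningfully. A scale that leaves some events without a grade forces ad hoc decisions. A top grade limited to life-threatening events gives a low severe count partly by construction. Separately, three sentences attach leaving the study to three different labels, and the article does not say how those labels relate.

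**Working it through.** There is no figure to reproduce. The check sets the sentences of section 2.9 side by side.

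**Step 1: trigger, definition and consequence of each label**

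| Label | Defined in section 2.9? | Consequence for participation |
|---|---|---|
| Mild | Yes: tolerable, and no specific intervention, and no effect on trial progress or prognosis | None |
| Moderate | Yes: clinically significant symptoms, hard to tolerate | Discontinuation or treatment is possible, not mandatory |
| Severe | Yes: life-threatening, with possible permanent disability or death | Immediate termination and emergency care |
| Serious | No | Prompt reporting and mandatory withdrawal |

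Three labels carry an exit consequence, each worded differently, and no sentence connects *serious* to any grade.

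**Step 2: does the scale cover every event?** Each test case is run through the definitions exactly as printed.

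- *A tolerable event that needs treatment*, for example a mild allergic reaction that is treated. It is not mild, because mild requires "symptoms that are tolerable to participants, requiring no specific intervention". It is not moderate, because moderate requires that the symptoms be hard to tolerate. It is not severe, because it does not threaten life. It has no grade, although allergic reaction is a risk that the section itself names.
- *An incapacitating event that does not threaten life.* It is not mild. It fits moderate. It cannot be severe. Moderate is its ceiling, however intense it is.
- *A liver or kidney finding without symptoms*, also a named risk. Mild and moderate are both worded in terms of symptoms, so read literally it fits neither unless it is life-threatening. This case is weaker than the first, because a reader could stretch mild to cover a finding that needs no action.

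**Step 3: effect on counts.** Under a scale graded by intensity, events of the second kind would be counted as severe. Under section 2.9 they are counted as moderate. To the extent that such events occur, the severe count is too low. The same definitions apply to every arm, so the shortfall arises in every arm. Events of the first kind have no defined place and will go wherever each investigator puts them.

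**Step 4: effect on withdrawal.** If *serious* is taken to mean *severe*, only life-threatening events make withdrawal mandatory. If *serious* is a separate category, some events graded below severe do so as well. The article does not say which reading is meant.

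**Step 5: size.** The article gives no adverse event rates, so the number of events misgraded or of patients affected cannot be calculated from it.

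**The case against.** The best defence has three parts.

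First, *serious adverse event* is a standard term, and a condensed article may leave its criteria to the full protocol or the case report form. That stands: the missing definition alone would not be a finding. It does not rescue the grade definitions, which the article does print and which are faulty as printed.

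Second, the two paragraphs can be read as two axes. Every life-threatening event is serious in the ordinary sense. A serious event of moderate grade falls under the withdrawal rule, and the possible discontinuation attached to moderate events does not conflict with that. This also stands. A reader might infer that section 2.9 strictly contradicts itself on who is withdrawn, but the text does not force that conclusion. What remains is that no sentence states the two-axis reading, and that the severity axis it relies on is itself defined by seriousness outcomes and leaves gaps.

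Third, every adverse event is to be documented and passed promptly to the supervising physician whatever its label. So internal documentation and escalation do not depend on the labels. Grading, onward reporting and withdrawal still do.

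It can also be said that separate tabulation and an extra box are merely good practice. That is fair for the tabulation. Closing the gap between mild and moderate is a correction.

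**Conclusion.** The point holds as a fault in the printed grading scale and in its unstated link to the withdrawal rule. Read as written, section 2.9 leaves tolerable events that need treatment without a grade, holds incapacitating but non-life-threatening events at moderate, and so understates severe events in all arms and invites inconsistent grading. The conclusion rests on the wording alone. Its size is unknown, because no event rates are given, and any percentage of affected patients would be invented.

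Two stronger readings are tempting and are not supported:

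- A reader might infer that withdrawn patients stop contributing MoCA at weeks 4 and 8. The article does not say whether assessments continue after withdrawal, so loss of primary-outcome data is an inference and not a stated consequence.
- A reader might infer that the narrow definition of severe flatters the EA, HOT and combination arms, since the Discussion presents these treatments as having few side effects. The same scale applies to every arm, including the donepezil control, so an arm-specific bias is not shown.

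This is a modest point with a cheap repair, and it is worth making before events are graded.

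**What to change.** - Define the severity grades by intensity only, with categories that meet and cover every event, including tolerable events that need treatment and findings without symptoms.
- Define *serious* once, by outcome criteria, and record it separately as yes/no on the case report form. Use that single term for the prompt-reporting rule.
- Reconcile the sentences that tie leaving the study to moderate, serious and severe events, so that the reader can tell which label triggers what. Which threshold is clinically right is for the sponsor to decide.
- Tabulate severity and seriousness separately by arm.

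The cost is revised wording in section 2.9 and one tick-box on the case report form, with no extra patients or procedures. The small downside is that some events now graded moderate would be reported as severe or serious.

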### Quality Control

2.10

Experienced and licensed physicians and therapists will administer interventions after receiving regular two‐day training sessions on treatment options. Standard operating procedures (SOPs) will be developed for participant screening, randomization, blinding, and manipulation to ensure consistency among investigators.

### Data Analysis

2.11

Researchers who are blind to the groupings will conduct data management and statistical analysis on the data acquired using the statistical software SPSS 22.0 (SPSS Inc., Chicago, IL, United States). Descriptive statistics will be utilized to depict the baseline characteristics of the two participant groups, with mean ± standard deviation for normally distributed continuous data and median and quartiles for non‐normally distributed continuous data. The normality of the data will be assessed using the Shapiro–Wilk test, and the homogeneity of variance will be assessed using the Levene test. One‐way analysis of variance (ANOVA) will be used for comparisons among multiple groups for normally distributed continuous data, while repeated measures analysis of variance will be used for within‐group pre‐ and post‐treatment comparisons. The Kruskal–Wallis test will be employed for non‐normally distributed continuous data. The significance level (α) for the statistical hypothesis tests will be set at *p* < 0.05, one‐tailed.

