**FIGURE 1 brb370631-fig-0001:**
[figure not shown]
Flow diagram of the study.

The sample size for this study will be calculated using the formula for a superiority trial of two independent sample sizes. Clinical experience and preliminary research indicated an effective rate of 90% in the treatment group and 80% in the control group (Hei et al. 2023, Su et al. 2023, Zhang et al. 2023). Based on these data, we conducted a sample size calculation using a two‐tailed *t*‐test with the following parameters: test boundary value *δ* = 0.15, significance level *α* = 0.025, and power *β* = 0.20 (Zabor et al. 2020). The calculation was performed using the following formula.

$$n=\left[{\left(Z_{\alpha /2}+Z\beta \right)}^{\wedge 2}*\left(p1\left(1-p1\right)+p2\left(1-p2\right)\right)\right]/{\left(\delta -|p1-p2|\right)}^{\wedge 2}$$

Considering a case number ratio of k = 1 between groups, the calculated sample size was 32 cases per group. To account for a potential 10% dropout rate, we increased the sample size to approximately 35 cases per group (International Council for Harmonisation of Technical Requirements for Pharmaceuticals for Human Use 1998). The total sample will be divided into 6 groups: control, EA, HOT, combination therapy, sham therapy, or the healthy, totaling around 210 cases to be included.

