Our research aims to evaluate the improvement of cognitive function in individuals with PSCI using different treatment methods. We have selected MoCA as the primary outcome measure for this study. MMSE and MBI is used as secondary outcome measures. The MoCA is another rapid screening tool for cognitive impairment, particularly sensitive to mild to moderate impairments, covering a wider range of cognitive domains comprehensively (Pinto et al. 2019). It includes more extensive memory tests by increasing the number and difficulty of words, extending the delay in recall, and providing a more accurate reflection of participants’ memory status. However, it requires more time compared to the MMSE. The MMSE is the most widely used dementia screening scale globally, focusing on cognitive abilities including orientation, memory, attention, calculation, recall, and language. It is a simple tool that aids in initial screening and categorizes participants based on their education level, with higher scores indicating stronger cognitive abilities, classified as normal, mild cognitive impairment, and dementia (Creavin et al. 2016). The ultimate goal of improving cognitive function is to reintegrate patients into their families and society. The MBI assesses daily living abilities in areas such as grooming, bathing, feeding, toileting, dressing, bowel and bladder control, stair climbing, transferring, walking on level surfaces, and wheelchair use. It provides different levels of ratings and reflects participants’ capabilities in daily activities (Liu et al. 2020).

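### The between-arm test of MoCA is gated on a Shapiro–Wilk result, so the primary effect measure (means or ranks) is not fixed in advance and can differ between weeks 4 and 8

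*Protocol article*

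**What the plan says.** Section 2.11 (Data Analysis) of the protocol article sets a two-stage procedure.

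- Stage one: "The normality of the data will be assessed using the Shapiro–Wilk test, and the homogeneity of variance will be assessed using the Levene test".
- Stage two, normal data: one-way ANOVA "will be used for comparisons among multiple groups for normally distributed continuous data".
- Stage two, non-normal data: "The Kruskal–Wallis test will be employed for non‐normally distributed continuous data".
- Within arms: "repeated measures analysis of variance will be used for within‐group pre‐ and post‐treatment comparisons".

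The Discussion (section 3) says: "We have selected MoCA as the primary outcome measure for this study". Primary Outcomes (section 2.7.1) schedules it at "baseline (week 0), during treatment (week 4), and follow‐up (week 8"). The section on data analysis does not mention MoCA by name. Since the article gives no other between-arm analysis, the general rule is the one that applies to it. The significance level "will be set at *p* < 0.05, one‐tailed".

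**The concern.** ANOVA compares mean scores. Kruskal–Wallis compares rank distributions. They answer different questions, and only the first leads directly to a benefit in MoCA points. The stated aim is to show that the combination is superior to each single treatment, and a reader will want to know by how many points. Under the rule in section 2.11, whether the primary comparison is of means or of ranks is known only after the outcome has been tested for normality. MoCA is analysed at two post-baseline visits, so one visit could be reported as a comparison of means and the other as a comparison of ranks. At stake is a primary effect measure fixed in advance and, to a smaller degree, the significance call in a borderline trial.

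**Working it through.** The article gives no figure on this point to reproduce. The only number taken from it is the arm size of 32 (section 2.1). It gives no MoCA mean, SD or shape, so these are assumptions: five patient arms of 32, whole-number scores limited to 0–30, mean 17, SD 3 to 5, shape normal or moderately left-skewed, Shapiro–Wilk at 0.05. Both omnibus tests were read at p < 0.05.

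**1. How often is the rank route taken?** If each arm is tested and any failure triggers the switch, exactly normal continuous data give 1 − 0.95^5 = 1 − 0.774 = 22.6%. Simulation gave 22.7%. Rounding to whole numbers raises this, more so at small SD. Testing pooled residuals is a single test, so it switches far less often.

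| Scores | Any arm fails | Pooled residuals |
|---|---|---|
| Near normal, SD 3–5 | 25–43% | 4–10% |
| Moderate skew (SD 4.5) | 97% | about 100% |

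**2. Can the two visits diverge?** Take normal whole-number scores, SD 4.5, a correlation of 0.7 between weeks 4 and 8 (assumed) and the any-arm rule. The visits took different routes in 41% of simulated trials. As a check, at 29.3% per visit and with independent pretests, 2 × 0.293 × 0.707 = 41.4%.

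**3. Does the gate protect the type I error?** With no true difference, fixed ANOVA rejected in 3.7–5.4% of trials across normal to moderately skewed shapes, and the two-stage rule in 4.1–5.5%. With 2,000 trials per scenario the standard error is √(0.05 × 0.95 / 2000) ≈ 0.5 percentage points. Neither procedure is materially off 5%, so the pretest is not needed.

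**4. How often does the gate change the result?** The relevant quantity is how often the two-stage call differs from that of fixed ANOVA. With one arm 3 points better:

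| Scores | Any arm fails | Pooled residuals |
|---|---|---|
| Near normal, SD 3–5 | about 0.5–1.7% | about 0.2–0.4% |
| Moderate skew | about 1–8% | about 1–8% |

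A rough check uses a separate run (SD 4.5, arm means 17/18/18/20/17). With normal whole-number scores the gate fired in 27.4% of trials and the two tests disagreed in 7.6%. If these were unrelated, 0.274 × 0.076 = 2.1%, the same order. With moderate skew, 0.971 × 0.107 = 10.4%. Other runs under the same kinds of assumption reached 2.1% for near-normal scores and 11% under marked skew, so the ranges are approximate.

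**5. What does a fixed mean-based test cost?** Under skew at SD 5, power was about 65% for ANOVA and 68% for Kruskal–Wallis. Other runs gave 51% against 54% and, at the largest gap, 67% against 73%.

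**The case against.** The strongest reply is that the rule is written in advance and applied by analysts blind to group, that both tests are valid, and that the practical effect is small. Most of this stands. A prespecified algorithm is not discretionary choice, the type I error is sound, and in near-normal data the gate rarely alters the call. It does not, however, fix the effect measure, and no amount of blinding would.

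Several stronger readings are tempting, and the document does not support them.

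- *That chance decides which test is reported.* This fits only near-normal scores, and the 25–43% needs an any-arm rule that the article does not state. Under real skew the shape of the scores decides, almost every time.
- *That the result is at risk in 7–9% of trials.* That is how often the two tests disagree whether or not the gate fires. It overstates the gate's effect in near-normal data.
- *That the switch removes the confidence interval or baseline adjustment.* The ANOVA branch as written names no covariate, contrast or interval either, and a rank test does not prevent mean differences from being reported.
- *That a pooled-variance ANOVA will be used despite unequal variances.* The article lists Levene's test without a consequence, and the action may be left to the analysis plan. With equal arms the effect is small in any case: four arms at SD 4 and one at SD 6, 32 each, gave a type I error of 5.5%.

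What exactly is tested (arm, pooled data or residuals) is a detail that an analysis plan may settle. The gate itself is not such a detail, because the article states it.

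**Conclusion.** The point holds as a defect in a stated rule, worth correcting but not one that invalidates the trial. Section 2.11 leaves the primary effect measure for MoCA to a normality pretest that is not needed for validity, and it allows weeks 4 and 8 to be analysed on different scales. The loss is a prespecified effect in MoCA points. Type I error is not materially affected, and the effect on the significance call is small near normality and modest under skew. All these sizes rest on assumed means, SDs and shapes, and on an assumed pretest threshold of 0.05. The conclusion that the effect measure is not fixed in advance follows from the text alone.

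**What to change.** In section 2.11, remove the Shapiro–Wilk result as a gate for MoCA. Name one mean-based between-arm model in advance, used whatever the normality test shows. A baseline-adjusted linear or mixed model, with standard errors that do not assume equal variances, would serve. State that the MoCA-point difference and its confidence interval will be reported on the same scale at weeks 4 and 8. Keep Kruskal–Wallis as a sensitivity analysis.

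The cost is a change of wording, with no extra patients or visits. The statistical price is a few percentage points of power if the scores prove markedly skewed.
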